	Patients with a vena cava filter in place
	Patients who have had a D–dimer test performed within 2 months of potential enrolment other than for evaluation for suspected recurrent VTE that was not confirmed
	Patients whose GP expects their life expectancy to be less than 5 years
	Patients unable to attend follow up visits due to geographic inaccessibility
	Patients participating in a competing investigation
	Patients with known antiphospholipid syndrome
	If patients are subsequently found to have antiphospholipid syndrome then they will have to be excluded.
	Patients with known inherited protein C and/or protein S or antithrombin deficiency
	If patients are subsequently found to have protein C and/or protein S or anithrombin deficiency then they will have to be excluded.
	Patients with a diagnosis of active cancer
	Patients unwilling to give consent

Those patients who reply with a positive response from willing general practices will be contacted to determine that they still wish to take part in the study. If still willing to take part then the research nurse or a member of the practice staff will access the patients’ primary care notes to assess their eligibility for inclusion into the study. If the patient is eligible then they will be followed up (at least 1 month before the end of their current treatment) to arrange their first visit to the GP surgery. Any additional travel costs and prescription costs will be paid to the patient from study funds.

Those with a negative reply will not be contacted. Those patients who do not return their postcard will be given a second postcard a month after the first one was given out. If a patient wishes to take part in the study but their GP is unwilling, alternative arrangements will be made at a hospital clinic.

The first appointment at the GP clinic will inform as to the nature of the trial. For those patients willing to participate the research nurse will obtain written informed consent.

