### Trial intervention

Study participants will have a total of six visits over a two year period.

#### Visit 1

This is the same visit as the information, consent and randomisation visit and will be within 2 weeks of current anticoagulation treatment end date. Patients will be randomised electronically into one of two groups; Group O will discontinue warfarin after their usual clinical intervention, Group W will continue warfarin for a further two years.

Patients will be interviewed to collect the following data:

Concomitant medications; ethnicity; smoking status; alcohol consumption; medical history; BMI; and family history of VTE

A heparinised venous sample of blood will be taken for a D-dimer test on a POC device (Cobas h 232, Roche diagnostics). In addition citrated venous samples will be collected for D-dimer testing. These will be sent to a central laboratory to be frozen and stored for analysis during and at the end of the study.

The D-dimer result will be recorded centrally onto a database for future analysis and both patient and researcher will be blinded as to the result of this test.

All patients will be clinically examined for signs and symptoms of PTS using a validated clinical scoring system (the Villalta scale) and will also complete the VEINES quality of life score [24] as well as EQ 5D which allows the measurement of broad aspects of quality of life [25]. In addition the patients will complete a costs questionnaire relating to the expenses incurred on a recent anticoagulation clinic visit. Where questionnaires are incomplete or unclear the patients will be contacted by telephone to clarify and complete the responses.

Compression stockings will be used by patients as advised by the clinician treating the DVT and the researchers will not influence their utilisation.

The anticoagulation clinic that the patient would normally attend will be informed that the patient is entering a study as will any specific hospital consultants who are involved with the patients’ care (e.g. haematologists). Patients randomly allocated to Group W will be followed-up through their usual oral anticoagulation service provided in terms of warfarin management and the anticoagulation clinic lead will be asked to extend their clinic visits for a further 2 years. Patients randomly allocated at this point to Group O will undergo a further D-dimer test 1 month after cessation of treatment. Again both researcher and patient will be blinded to this result.

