#### Visits 2–6

All patients randomised (Groups W and Group O) will be reviewed every 6 months for 2 years in total to assess evidence of VTE recurrence, clinical assessment of PTS, and measurement of D-dimer (again patient and researcher are blinded to these results).

All patients will again be asked to complete the VEINES-QOL/Sym a validated disease specific, quality of life score, and EQ 5D, questionnaires.

If a patient in Group O (off warfarin) has their warfarin restarted by their GP during the study period for a VTE recurrence then they will be removed from the study but a case review will be carried out in patient’s primary care notes looking for evidence of thrombotic events. If a patient in Group O has to restart warfarin for another reason e.g. atrial fibrillation, then they will continue to be followed up in the usual manner. If a patient in Group W (on warfarin) has to permanently stop taking their warfarin during the study then they will be followed up and included in the final analysis on an intention to treat basis. If a patient in Group W has a temporary break in their treatment for any reason, they will continue to follow the same visit regime, making a note of the temporary break.

Patients in Group W will be asked to return for a final D-dimer test 1 month after discontinuing warfarin.

Patients randomised into group W will continue with their warfarin management as before. INR data will be collected from the anticoagulation database at six monthly intervals throughout the study to assess overall control.

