Total sample size will be sufficiently large to show a significant difference in recurrence rates between those showing a positive D-dimer on treatment who receive warfarin (RW) and those showing a positive D-dimer who receive no treatment (RNO plus RRO). Following Palareti [7] this means a sample size for each group of 79 in order to give 90% power to a 5% significance test when comparing 2 year recurrence rates of 21.4% and 4.3%. Assuming a 50% positive D-dimer rate this implies a total of 79 × 2 × 2/0.9 = 352 patients taking part in the study (and 316 completing the study). Allowing a 50% participation rate this means that 704 patients need to be approached initially. With such a sample size an overall comparison of recurrence rates between the arms W and O can be made with power of between 86 and 99% assuming recurrence rates of between 1.4% and 4.3% for the warfarin arm (Group W, depending on what recurrence rate patients with normal D-dimer on warfarin produce) and 14.2% for the No treatment arm.

One of the objectives of the study is to determine an optimal cut off on a D-dimer result taken when the patient is receiving treatment. In a study of 272 patients, Baglin *et al.* report that 170/272 patients had a D-dimer in excess of 500 ng mL-1 and their ROC analysis suggests an optimal cut off of 500 ng/ml [10]. The circumstances of their study differ from ours but using their data will give some indication of the precision with which we will be able to estimate an optimal cut off with slightly more patients than Baglin *et al.* With some assumptions, a rough calculation of the precision with which a cut off in the region of 500 could be estimated with our sample size of 316 would be within about 7% (95% confidence interval).

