### Analysis and statistical methods

Intention to treat analysis will be used. The types of analysis proposed are Chi-square, generalized linear models, logistic regression and survival analysis, t-tests, ANOVA and non-parametric equivalents.

Analysis will be carried out at the end of the study, as there is likely to be insufficient power for interim analyses. Quality control of data collection will be conducted by a trial management committee throughout the study and by a statistician independent of the research team.

Logistic regression would be used to relate D-dimer result and other patient data to events such as recurrence, bleeding episodes and PTS separately on the two arms (Group W and Group O) of the trial and together. Baglin *et al*[10], with their 272 patients, showed a significant association between age and D- dimer (p < 0.001) and our total sample, allowing for loss to follow up, of 316 should be ample to incorporate such a relationship. In comparing D-dimer levels between genders they achieved a significance level of p = 0.18 with 272 individuals. A rough calculation would suggest a p value of 0. 15 for the same level of difference in D-dimer (approximately 80 ng/ml) in our total sample of 316 patients.

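### Table 1 requires exclusion of patients later found to have antiphospholipid syndrome or an inherited deficiency; this can apply after randomisation and then conflicts with the unqualified intention-to-treat statement

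*Protocol article*

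**What the plan says.** The exclusion criteria in Table 1 (Participants) treat these conditions in two steps. The first is an ordinary entry criterion: "Patients with known antiphospholipid syndrome", and likewise known inherited protein C, protein S or antithrombin deficiency. The second is a separate sentence for each: "If patients are subsequently found to have antiphospholipid syndrome then they will have to be excluded" and "If patients are subsequently found to have protein C and/or protein S or anithrombin deficiency then they will have to be excluded".

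On timing, Participants has eligibility checked in the primary care notes before the first appointment. Trial intervention says of Visit 1: "This is the same visit as the information, consent and randomisation visit". The blood samples listed for that visit are for D-dimer.

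On analysis, Analysis and statistical methods says "Intention to treat analysis will be used" and names no exception. Visits 2–6 covers two other kinds of departure. Group W patients who stop warfarin permanently stay in: "then they will be followed up and included in the final analysis on an intention to treat basis". Group O patients restarted on warfarin for a recurrence leave, but their events are still sought: "then they will be removed from the study but a case review will be carried out". No such provision is made for patients excluded under the second step of Table 1.

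**The concern.** The second sentence for each condition adds something to the first only if it covers discovery after the entry check. Most of the time after that check lies after randomisation. The article describes no test applied to everyone, so whether a condition is found depends on whether someone looks for it in routine care. Read literally, the rule lets randomised patients be dropped on information that arises during follow-up, when allocation is known and outcomes may be known too.

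Excluding patients who were ineligible all along does little harm when everyone is assessed in the same way, blind to arm and outcome. The article describes neither safeguard for this exclusion. The independent committee is blinded to allocation, but its stated task is the cause of hospitalisation or death.

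At stake is a small number of events. If recurrences prompted the testing, the exclusions would fall mainly on recurrers, and most recurrers are expected in Group O. Removing them would make stopping warfarin look safer than it was in the randomised groups.

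**Working it through.** **Inputs (Sample size section).** Two-year recurrence in patients with raised D-dimer at randomisation is 21.4% without and 4.3% with warfarin, with 79 per group, a 5% test and 90% power. The total is 352 entering and 316 completing, with 10% loss to follow-up. For the whole arms the rates are 14.2% in Group O and 1.4% to 4.3% in Group W. The test is taken as two-sided, which the article does not state.

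**Step 1: reproduce the plan.** For two proportions with pooled variance under the null and no continuity correction:

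n = [1.960·√(2·p̄·(1−p̄)) + 1.282·√(p₁(1−p₁) + p₂(1−p₂))]² / (p₁−p₂)²

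With p₁ = 0.214, p₂ = 0.043 and p̄ = 0.1285:
- numerator: (1.960 × 0.4733 + 1.282 × 0.4576)² ≈ 2.292
- denominator: 0.171² = 0.02924
- n ≈ 78.4, rounded up to 79, as stated; power at 79 is 90.2%.

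The total is 79 × 2 × 2 / 0.9 = 351.1, rounded up to 352. With 158 per arm, the overall comparison has power 86.3% (14.2% vs 4.3%) and 99.1% (14.2% vs 1.4%), matching the stated range. The plan's arithmetic is sound, and this point does not rest on an error in it.

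**Step 2: expected events.** Raised-D-dimer Group O: 79 × 0.214 = 16.9. Group RW: 79 × 0.043 = 3.4.

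**Step 3: one-sided illustration.** Suppose k patients are excluded, all of them raised-D-dimer Group O recurrers and none from Group W. The Group O rate becomes (16.9 − k)/(79 − k). Power is recomputed with the same test against 4.3% in 79. The overall comparison uses (22.4 − k)/(158 − k), where 158 × 0.142 = 22.4, against 158 in Group W.

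| k | Group O rate, raised D-dimer | Difference from 4.3% (points) | Power, raised D-dimer | Overall power, W at 4.3% | Overall power, W at 1.4% |
|---|---|---|---|---|---|
| 0 | 21.4% | 17.1 | 90% | 86% | 99% |
| 1 | 20.4% | 16.1 | 87% | 83% | 99% |
| 2 | 19.4% | 15.1 | 84% | 79% | 98% |
| 3 | 18.3% | 14.0 | 79% | 75% | 98% |

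Here k = 3 means that 3/16.9, or about 18%, of the expected Group O recurrers would be found to have one of these conditions. Nothing in the documents says whether that is likely. The 10% allowance is for loss to follow-up; no separate allowance is made for exclusions.

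**Step 4: set the rules side by side.** Group W patients who stop warfarin are followed and analysed as randomised. Group O patients restarted for recurrence are removed, with a records review for thrombotic events. Patients diagnosed later under Table 1 are excluded, with no statement on follow-up, records review or analysis. Only this last group is left to a rule that, taken literally, overrides intention to treat.

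**The case against.** The strongest reply is that the text is ambiguous rather than wrong. The sentences sit in an eligibility table, and exclusion is not defined there as leaving treatment, follow-up or analysis. Screening has several stages: the notes check, the history taken at Visit 1, and a physician's sign-off (Assessment of safety). A diagnosis could therefore come to light before randomisation. The article is also condensed, and the full protocol or analysis plan may define the analysis set.

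The ambiguity is real, but it does not remove the conflict. Nothing confines the rule to the interval before randomisation, and nothing keeps these patients in. The objection concerns two statements in the article that do not fit together, not a detail missing from it.

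Other parts of the reply stand and limit the point. A reader might infer the following, none of which the documents support:
- *That exclusion will be linked to outcome and arm.* Nothing says what prompts testing or that it differs by arm. Work-up of the index event fits the text equally well.
- *That recorded recurrences will be deleted.* GP records are reviewed six-monthly for thrombotic events, and Group O patients restarted for recurrence get a case review. The harm requires a further step that the article leaves open but does not prescribe.
- *That Group O as a whole expects five times the recurrences of Group W.* That ratio (21.4/4.3 ≈ 5) holds for raised-D-dimer patients only. For the whole arms it runs from 14.2/4.3 ≈ 3.3 to 14.2/1.4 ≈ 10.
- *That the bias could never be assessed.* If exclusions are counted by arm, worst-case bounds can be calculated.

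**Conclusion.** The concern holds in this form: the rule as written can remove randomised patients, it conflicts with the unqualified intention-to-treat statement, and nothing in the article says that these patients stay in follow-up or analysis. This conclusion needs no assumption about prevalence or testing.

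The bias is conditional. If discovery is prompted by recurrence, exclusion would fall mainly on Group O and pull the comparison towards no difference. In the one-sided illustration, 1, 2 or 3 such exclusions lower power in the raised-D-dimer comparison from 90% to 87%, 84% or 79%. These figures show how few events the comparison rests on. They do not forecast this trial's loss, because the documents give neither a prevalence nor a testing rate, and the illustration assumes that no one else is excluded. Keeping every randomised patient leaves the stated design as it is: 79 per group, 352 in total, 90% power.

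**What to change.** In Table 1, limit both exclusions to conditions known before randomisation. Replace the two sentences on later discovery with a statement that patients identified after randomisation remain in follow-up and in the intention-to-treat analysis as randomised. Report the number identified later by arm, and add a sensitivity analysis that omits them. State that how these patients are treated is a matter for their clinicians and does not determine whether they are followed or analysed.

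The cost is two sentences in Table 1, one line of reporting and one sensitivity analysis, with no change to the sample size. The change should be made before the rule is applied to anyone, since follow-up that was not collected may not be fully recoverable later.

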### Trial intervention

Study participants will have a total of six visits over a two year period.

#### Visit 1

This is the same visit as the information, consent and randomisation visit and will be within 2 weeks of current anticoagulation treatment end date. Patients will be randomised electronically into one of two groups; Group O will discontinue warfarin after their usual clinical intervention, Group W will continue warfarin for a further two years.

Patients will be interviewed to collect the following data:

Concomitant medications; ethnicity; smoking status; alcohol consumption; medical history; BMI; and family history of VTE

A heparinised venous sample of blood will be taken for a D-dimer test on a POC device (Cobas h 232, Roche diagnostics). In addition citrated venous samples will be collected for D-dimer testing. These will be sent to a central laboratory to be frozen and stored for analysis during and at the end of the study.

The D-dimer result will be recorded centrally onto a database for future analysis and both patient and researcher will be blinded as to the result of this test.

All patients will be clinically examined for signs and symptoms of PTS using a validated clinical scoring system (the Villalta scale) and will also complete the VEINES quality of life score [24] as well as EQ 5D which allows the measurement of broad aspects of quality of life [25]. In addition the patients will complete a costs questionnaire relating to the expenses incurred on a recent anticoagulation clinic visit. Where questionnaires are incomplete or unclear the patients will be contacted by telephone to clarify and complete the responses.

Compression stockings will be used by patients as advised by the clinician treating the DVT and the researchers will not influence their utilisation.

The anticoagulation clinic that the patient would normally attend will be informed that the patient is entering a study as will any specific hospital consultants who are involved with the patients’ care (e.g. haematologists). Patients randomly allocated to Group W will be followed-up through their usual oral anticoagulation service provided in terms of warfarin management and the anticoagulation clinic lead will be asked to extend their clinic visits for a further 2 years. Patients randomly allocated at this point to Group O will undergo a further D-dimer test 1 month after cessation of treatment. Again both researcher and patient will be blinded to this result.

#### Visits 2–6

All patients randomised (Groups W and Group O) will be reviewed every 6 months for 2 years in total to assess evidence of VTE recurrence, clinical assessment of PTS, and measurement of D-dimer (again patient and researcher are blinded to these results).

All patients will again be asked to complete the VEINES-QOL/Sym a validated disease specific, quality of life score, and EQ 5D, questionnaires.

If a patient in Group O (off warfarin) has their warfarin restarted by their GP during the study period for a VTE recurrence then they will be removed from the study but a case review will be carried out in patient’s primary care notes looking for evidence of thrombotic events. If a patient in Group O has to restart warfarin for another reason e.g. atrial fibrillation, then they will continue to be followed up in the usual manner. If a patient in Group W (on warfarin) has to permanently stop taking their warfarin during the study then they will be followed up and included in the final analysis on an intention to treat basis. If a patient in Group W has a temporary break in their treatment for any reason, they will continue to follow the same visit regime, making a note of the temporary break.

Patients in Group W will be asked to return for a final D-dimer test 1 month after discontinuing warfarin.

Patients randomised into group W will continue with their warfarin management as before. INR data will be collected from the anticoagulation database at six monthly intervals throughout the study to assess overall control.

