#### Patient quality of life

This will be assessed by all patients completing questionnaires at each study visit.

Veines-QOL/Sym a validated disease specific quality of life questionnaire will be used as well as EQ-5D allows changes in health status to be measured but also valued, using the University of York Measurement & Valuation of Health general population survey tariff. Where questionnaires are incomplete or unclear the patients will be contacted by telephone to clarify and complete the responses.

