#### Cost data

The cost analysis will adopt a broad perspective to include costs incurred within the health sector and by patients. Health sector costs will include additional costs of D-dimer testing and prolonged treatment (anticoagulation) costs. Patient level data will be collected on treatment and condition-specific health service utilisation (primary and secondary care), thrombotic episodes, PTS and bleeding events. Information on costs incurred by patients when attending anticoagulation clinics (e.g. time and travel costs) will also be collected with a patient cost questionnaire. Information on resource use will be collected from patient notes. Unit costs will be obtained from standard sources and health care providers.

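### Group O patients who restart warfarin for a recurrent VTE leave follow-up, so PTS, quality-of-life and non-admitted bleeding data after recurrence are lost in one arm only

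*Protocol article*

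**What the plan says.** The Visits 2–6 section of the protocol article treats four situations.

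- **Group O, warfarin restarted for a recurrence.** Patients whose warfarin is "restarted by their GP during the study period for a VTE recurrence then they will be removed from the study". What continues is a case review of the "primary care notes looking for evidence of thrombotic events".
- **Group O, warfarin restarted for another reason** (atrial fibrillation is the example given): "then they will continue to be followed up in the usual manner".
- **Group W, warfarin stopped permanently:** "then they will be followed up and included in the final analysis on an intention to treat basis".
- **Group W, recurrence:** no specific rule.

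The same section opens by saying that all randomised patients in both groups "will be reviewed every 6 months for 2 years in total to assess evidence of VTE recurrence, clinical assessment of PTS". Analysis and statistical methods states: "Intention to treat analysis will be used". On quality of life, the protocol says: "This will be assessed by all patients completing questionnaires at each study visit". On costs, it says: "Information on resource use will be collected from patient notes".

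**The concern.** Removal is triggered by the event that the trial is designed to count, and it is written for one arm only. A patient who has left has no further visits, and the visits are where the Villalta score, VEINES and EQ-5D are obtained. The review that continues is limited to thrombotic events, so it does not look for bleeding after warfarin is restarted.

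Reducing PTS is part of the first aim, and PTS severity, bleeding, quality of life and cost-effectiveness are secondary outcomes. If recurrence worsens PTS and quality of life, the consequences of stopping warfarin fall mainly on the patients whose later follow-up ends. Group O would then look better than it is on those outcomes. Bleeding on restarted warfarin would also be under-counted in Group O. No analysis plan can restore assessments that were never made.

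**Working it through.** **The plan's own figures** (Sample size section). Two-sided 5% test, pooled variance, no continuity correction, 21.4% v 4.3%, 90% power:

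n = [1.960 × √(2 × 0.1285 × 0.8715) + 1.282 × √(0.214 × 0.786 + 0.043 × 0.957)]² / 0.171² = 78.4, so 79 per group, as stated.

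79 × 4 = 316 completing, and 316 / 0.9 = 351.1, so 352 randomised. With 158 per arm, the overall comparison has power 86.3% (14.2% v 4.3%) and 99.1% (14.2% v 1.4%), matching the stated 86 to 99%. None of these figures is in dispute.

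**How many patients the rule reaches**, using the same rates and assuming that every recurrence leads to a restart:

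| Group | Calculation | Patients |
|---|---|---|
| O, completers | 0.142 × 158 | 22.4 |
| O, randomised | 0.142 × 176 | 25.0 |
| O, raised D-dimer | 0.214 × 79 | 16.9 |
| W, recurrences, low | 0.014 × 158 | 2.2 |
| W, recurrences, high | 0.043 × 158 | 6.8 |

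The 14.2% is larger than the 10% loss to follow-up that the plan allows for and, unlike ordinary loss, depends on the outcome.

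**What is lost after the recurrence in Group O**

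- Villalta, VEINES, EQ-5D: lost, because they are collected at visits.
- Bleeds without admission: largely lost, because the case review names thrombotic events only.
- Bleeds with admission: partly recoverable, because GP records are searched six-monthly for hospital admissions.
- Costs: partly recoverable, because resource use comes from notes.
- Thrombotic events: largely kept. The triggering event is already known and later ones are sought.

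**Illustration for PTS.** All three inputs are assumptions: PTS risk q = 25% without recurrence; risk multiplied by k after recurrence; removed patients contribute no PTS outcome. The protocol's 25% is an overall 2-year cumulative incidence after DVT; it gives no recurrence-free rate. With recurrence rates r:

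- true difference O − W = q(k − 1)(r_O − r_W)
- observed difference = −q(k − 1) r_W, because Group O is left with q

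For k = 2:

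- r_W = 1.4%: true 0.25 × 0.128 = +3.2 points; observed −0.25 × 0.014 = −0.35, about −0.4
- r_W = 4.3%: true 0.25 × 0.099 = +2.5 points; observed −0.25 × 0.043 = −1.1

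At r_W = 4.3%, k = 1.5 gives true 0.125 × 0.099 = +1.2 and observed −0.125 × 0.043 = −0.5. With k = 3 the figures are 0.50 × 0.099 = +5.0 and −0.50 × 0.043 = −2.2.

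**Scale against chance.** With 158 per arm and PTS near 25%, the standard error of the difference is √(2 × 0.25 × 0.75 / 158) = 4.9 points. For k = 2 the shift is 0.25 × 0.142 = 3.55 points, about 0.7 standard errors.

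**The case against.** Much can be said for the plan, and several stronger readings do not hold.

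- **A reader might infer that the primary comparison is biased.** The documents do not support this. Both primary outcomes count recurrent thrombotic events, the triggering event has already occurred, further events are looked for, and deaths are flagged and adjudicated blind.
- **A reader might infer that removed patients' earlier data are deleted.** The text does not say so. Keeping scores from before the recurrence confines the loss to the later period. It would shrink the PTS shift so far as those scores already show PTS above the recurrence-free rate, but would not capture PTS arising afterwards.
- **A reader might infer that these patients are excluded from the intention-to-treat analysis.** Removal could mean only leaving the visit schedule. Even so, inclusion in the final analysis is spelled out only for Group W patients who stop, and six-monthly review is promised for everyone randomised. The passages need reconciling.
- **A reader might infer that costs disappear from Group O.** They need not: resource use is taken from notes, and the Cost effectiveness analysis section intends collection for all trial patients and allows imputation. Imputing EQ-5D is harder, because no Group O patient removed under the rule would supply later scores and Group W would have only 2 to 7 recurrences to learn from.
- **The 22 removals are an upper figure.** Background describes long-term warfarin as normal after recurrence only where it is not contraindicated, and a fatal recurrence leads to no restart.
- **Retention of Group W recurrers is read from silence**, supported by the general statement that all randomised patients are reviewed.

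What stands is a one-arm, outcome-triggered loss of visit-based data and non-admitted bleeds after recurrence.

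**Conclusion.** The concern holds for PTS, quality of life and QALYs, and bleeding not leading to admission. It holds in part for costs, and it leaves the primary recurrence outcome largely intact. Up to about 22 of 158 Group O completers (up to about 17 of 79 with raised D-dimer) would lose later follow-up, against no stated removal among about 2 to 7 Group W recurrences.

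The direction of the PTS bias needs only that recurrence raises PTS risk and that the later PTS goes unrecorded. Its size is not known from the documents. The illustrated change from +2.5 to +3.2 points to about −0.4 to −1.1 rests on the assumed 25% and doubling, on every recurrence leading to a restart, and on removed patients contributing no PTS outcome. It should not be read as a forecast that the trial's result will change sign: the shift is smaller than one standard error. It is systematic, however, and analysis cannot reliably repair it.

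**What to change.** In Visits 2–6, replace the removal rule with a statement that every randomised patient in both arms, whatever their recurrence or anticoagulation status, continues the six-monthly assessment of all outcomes (Villalta, VEINES, EQ-5D, bleeding, resource use) to 2 years and is analysed as randomised. Say explicitly that this covers a recurrence in Group W as well. Keep the notes review as a fallback for patients who decline further visits. The change concerns data collection only; treatment after a recurrence stays with the patient's clinicians.

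The cost is a protocol amendment and the remaining visits of about 22 patients, which are already in the schedule. The sample size does not change.
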